### 3. STUDY DESIGN

The RELIEF Study is a single-blinded (investigator-blinded) sham-controlled study to test the mechanisms and effectiveness of two manual therapy techniques applied to individuals (18-45 years of age) with chronic low back pain. There are two major goals of this study. One is to determine the biological mechanisms of two manual therapy interventions commonly used in the treatment of chronic low back pain (i.e., 'Mechanistic Component'). The second is to conduct a randomized clinical trial (RCT) to determine the effectiveness of these two manual therapies at reducing pain and disability in patients with chronic low back pain compared to each other as well as to a sham control group (i.e., 'RCT Component'). Accordingly, this study consists of three mechanistic experiments across which the clinical outcome variables will be pooled for an exploratory Phase II RCT investigating the effectiveness of manual therapies in treating chronic LBP.

A total of 162 individuals with chronic low back pain and 60 participants without low back pain will participate in the RELIEF Study. Forty-two individuals will be recruited and enrolled into Experiment 1 (Muscular Effects), sixty individuals with low back pain and 60 with no low back pain will be recruited and enrolled into Experiment 2 (Spinal Effects), and sixty individuals will be recruited and enrolled into Experiment 3 (Cortical Effects). Within each of these separate experiments, participants with chronic low back pain will be randomly assigned to one of the three treatment arms: 1) spinal manipulation, 2) spinal mobilization, or 3) sham Laser therapy. The clinical outcome data will be pooled across the three physiological experiments resulting in 54 subjects/treatment arm. Treatments will be delivered twice per week for 3-weeks. The primary outcomes for the Mechanistic and RCT components of the RELIEF Study are provided below:

#### Mechanistic Component

- Group 1 (Muscular Effects):
  - Skeletal muscle proton transverse relaxation time (T2) of the lumbar muscles.
- Group 2 (Spinal Effects):
  - Short-latency stretch reflex excitability.
  - Trunk muscle onset latencies in response to postural perturbations.
  - Lumbar motion during volitional movement tasks.
  - Dynamic trunk stiffness
- Group 3 (Cortical Effects):
  - Motor evoked potential amplitude.
  - Intracortical facilitation.
  - Short-interval intracortical inhibition.

#### RCT Component

##### Co-Primary Outcomes:

- Change in Numerical Pain Rating (NPR) score over the last 7-days
- Change in Roland Morris Disability Questionnaire (RMDQ)

##### Secondary Outcomes:

- Change in PROMIS Pain Behavior
- Change in PROMIS Pain Interference

- Change in PROMIS Pain Intensity
- Change in PROMIS Physical Function
- Change in NPR scores for current pain, and worst and best pain in the last 7-days

More information regarding the supplemental research study design is included in the appendix.

THE  
**RELIEF**  
STUDY

RESEARCHING THE EFFECTIVENESS OF LUMBAR  
INTERVENTIONS FOR ENHANCING FUNCTION

[figure not shown][figure not shown]

OHIO  
UNIVERSITY

[figure not shown]

OHIO MUSCULOSKELETAL  
AND NEUROLOGICAL INSTITUTE  
Heritage College of Osteopathic Medicine

### Target Populations and Study Groups:

Forty-two patients with chronic low back pain will be enrolled into experiment 1 (Muscular Effects) and randomly assigned to the following 3 treatment arms (14 patients per arm): 1) spinal manipulation, 2) spinal mobilization, or 3) sham Laser. Sixty patients with chronic low back pain will be enrolled into experiment 2 (Spinal Effects) and randomly assigned to the following 3 treatment arms (20 patients per arm): 1) spinal manipulation, 2) spinal mobilization, or 3) sham Laser. Sixty participants without low back pain will be enrolled into a modified experiment 2 (Spinal Effects). Sixty patients with chronic low back pain will be enrolled into experiment 3 (Cortical Effects) and randomly assigned to the following 3 treatment arms (20 patients per arm): 1) spinal manipulation, 2) spinal mobilization, or 3) sham Laser. Treatments will be delivered twice per week for 3-weeks. The clinical outcome data will be pooled across the three physiological experiments resulting in 54 subjects/treatment arm. The table below summarizes the enrollment plan.

| Experiment             | Treatment Arm |              |            | Healthy Control |
|------------------------|---------------|--------------|------------|-----------------|
|                        | Manipulation  | Mobilization | Sham Laser |                 |
| Muscular Effects       | 14            | 14           | 14         |                 |
| Spinal Effects         | 20            | 20           | 20         | 60*             |
| Cortical Effects       | 20            | 20           | 20         |                 |
| Σ of All Groups | 54            | 54           | 54         |                 |

\*Modified Spinal Effect experiment

Study Location: The primary site for the RELIEF Study will be at the Ohio Musculoskeletal and Neurological Institute's (OMNI) main facility on the 2nd floor West Wing of Irvine Hall. This is a laboratory-based facility designed for specifically for clinical research.

Study Duration: The study duration for an individual participant with low back pain is ~ 8 weeks. Specifically, we expect that the typical amount of time between the event of enrollment ascertainment and randomization will be 3-5 days (maximum 7), and that randomization will occur when study participants begin a study intervention (visit 2). The study intervention will occur over a 3-week period followed by approximately 4-week follow-up. Thus, in total the study duration for an individual participant will be ~ 8 weeks. Specifically, in the first visit we will obtain informed consent and conduct a screening exam to determine if candidates meet the inclusion/exclusion criteria for a given experiment. If subjects meet the inclusion/exclusion criteria for an experiment they will be enrolled into the study and allocated to one of three experimental measurement groups (i.e., Muscular, Spinal, or Cortical). At the second visit, participants will then be randomized to an intervention arm (i.e., mobilization, manipulation, or laser), baseline assessments of both clinical and physiological outcome measures will be obtained, a treatment intervention will be performed, and clinical and physiological outcome measures will be repeated (i.e., follow-up assessment). Participants will then undergo an additional five treatments over the next three weeks (visits 3-7; total treatments: 6; treatment frequency: 2x/week). It should be noted that following treatment 1 we will assess expectancy and credibility expectations for the respective treatment intervention. Three days +/- 1-day after the final treatment, subjects will report back to the laboratory for a follow-up assessment of the clinical and physiological outcome measures (visit 8). Lastly, to determine the long-term effects of the interventions, subjects will report back to the laboratory approximately 4 weeks (28-days +/- 4-days) after their last treatment for the final follow-up assessment of the clinical and physiological outcome measures.

(visit 9). The study duration for a participant in the healthy control group is 3-hour including screening, baseline assessments, and lab testing. The anticipated duration for the RELIEF Study is 5-years. We anticipate the total enrollment time to take up to 4 years (48 months). The required monthly enrollment rate for study completion in the proposed time frame is 3.4 subjects/month.

Randomization, Stratification, and Blinding:

- Randomization & Stratification: The study statistician will use the R statistical language to block-randomize treatments stratified by sex for each of the three separate experiments. Specifically, within each experiment there will be two strata within which we will create blocks of 3 patients, where treatments are permuted. Based on the randomization table the study coordinator will assign subjects to the treatment arms. In instances where multiple experiments are actively enrolling study participants and a participant meets eligibility requirements for more than one experiment, we will then use an adaptive randomization method to allocate them to one of the experiments. This method ensures that an experiment with fewer participants enrolled will have a higher allocation ratio. Specifically, with two potential experiments, the allocation ratio for Experiment  $i$  ( $p_i$ ) will be  $p_i = 1 - n_i/N$ , where  $n_i$  is the sample size for Experiment  $i$  and  $N$  is the total sample size thus far enrolled. With three active experiments, the allocation ratio will be  $p_i = (1 - n_i/N)/2$ . Note that this allocation to an experimental measurement group occurs prior to the randomization to a treatment arm.
- Masking or Blinding: In the RELIEF Study the principal investigators, the statistician, and members of the data collection team will remain blinded to intervention assignment throughout the duration of the study. They will be given the identifying codes only at the end of the study when it is necessary to interpret the results of the study. The un-blinded study coordinator, who is responsible for scheduling testing and treatment sessions, will serve to receive the study patients and escort them to the various testing and treatments sites to minimize the interaction between patients; however, the study coordinator will not participate in the assessments.

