participants are screened. Once the study is described in detail to a candidate, if the candidate continues to expresses interest in the study we will consent them prior to beginning the screening process. Participant is notified regarding end of active protocol participation during Visit 9.

Randomization Procedures: The study statistician will use the R statistical language to block-randomize treatments stratified by sex for each of the three separate experiments. Specifically, within each experiment there will be two strata within which we will create blocks of 3 patients, where treatments are permuted. The study coordinator will use this table to assign subjects to the treatment arms.

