## **5.2 Handling of Study Interventions**

Each subject will, of necessity, be aware of group assignment. However, study personnel who collect the outcome measures will be blinded to the subject's group assignment as will the PIs and the statistician.

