### Treatment Assignment Procedures

Randomization & Stratification: The study statistician will use the R statistical language to block-randomize treatments stratified by sex for each of the three separate experiments. Specifically, within each experiment there will be two strata within which we will create variable blocks of 3 or 6 patients, where treatments are permuted. Then the study coordinator will assign subjects to the treatment arms. In instances where multiple experiments are actively enrolling study participants and a participant meets eligibility requirements for *more than one experiment*, we will then use an adaptive randomization method to allocate them to one of the experiments. This method ensures that an experiment with fewer participants enrolled will have a higher allocation ratio. Specifically, with two potential experiments, the allocation ratio for Experiment  $i$  ( $p_i$ ) will be  $p_i = 1 - n_i/N$ , where  $n_i$  is the sample size for Experiment  $i$  and  $N$  is the total sample size thus far enrolled. With three active experiments, the allocation ratio will be  $p_i = (1 - n_i/N)/2$ . Note that this process would occur prior to the randomization to a treatment arm.

- Masking or Blinding: In the RELIEF Study the principal investigators, the statistician, and members of the data collection team will remain blinded to intervention assignment throughout the duration of the study. They will be given the identifying codes only at the end of the study when it is necessary to interpret the results of the study. The un-blinded study coordinator, who is responsible for scheduling testing and treatment sessions, will serve to receive the study patients and escort them to the various testing and treatments sites to minimize the interaction between patients; however, the study coordinator will not participate in the assessments.

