## Visit 1: ENROLLMENT AND RANDOMIZATION

*To be completed by study coordinator*

Is the participant eligible for the study based on inclusion and exclusion criteria?

- ☐ Yes (If yes, date enrolled \_\_\_\_\_ and randomized if different \_\_\_\_\_)  
Day-Month-Year Day-Month-Year
- ☐ No (If no, leave the rest of the form blank.)

If eligible and not randomized, indicate reason:

- ☐ Failed to return ☐ Declined participation
- ☐ Other (specify): \_\_\_\_\_

**Experiment Exclusion Section:** The candidate is **excluded** from participating in the following experiment(s):

- ☐ Experiment 1 (Muscular): MRI
- ☐ Experiment 2 (Spinal): Biomechanics
- ☐ Experiment 3 (Cortical): TMS

Participant is available\* for the following experiments:

- ☐ 1 Muscular - MRI
- ☐ 2 Spinal - Biomechanics
- ☐ 3 Cortical - TMS

\*Participant being "available" is based on: 1) meeting inclusion/exclusion criteria for a given experiment; 2) the experimental protocol being open to enrollment; and 3) the study participant and laboratory schedules align.

Participant assigned to Experiment:

- ☐ 1 Muscular - MRI
- ☐ 2 Spinal - Biomechanics
- ☐ 3 Cortical - TMS

Participant randomly assigned to Intervention Arm:

- ☐ 1 Manipulation
- ☐ 2 Mobilization
- ☐ 3 Laser

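### Sections 3 and 4.3 fix treatment blocks at 3 while section 9.2 varies them between 3 and 6; fixed blocks of 3 make one assignment in three certain, and no rule conceals the list from the coordinator

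*Supplement*

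**What the plan says.** The trial randomises to three arms within three experiments, stratified by sex: "block-randomize treatments stratified by sex for each of the three separate experiments". That makes six strata. The protocol describes the block rule three times.

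- **Section 3, Randomization and Stratification:** "within each experiment there will be two strata within which we will create blocks of 3 patients, where treatments are permuted".
- **Section 4.3, Randomization Procedures:** "we will create blocks of 3 patients, where treatments are permuted. The study coordinator will use this table to assign subjects".
- **Section 9.2, Treatment Assignment Procedures:** "within each experiment there will be two strata within which we will create variable blocks of 3 or 6 patients".

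Sections 3 and 4.3 have the coordinator assign arms from the randomisation table; section 9.2 also gives the task to the coordinator. Section 3 describes this role as unblinded and responsible for scheduling, and section 6.2.1 has the coordinator complete the screening forms with the candidate. Section 6.2.3 accepts that treatment providers cannot be blinded. Section 5.2 says of participants: "Each subject will, of necessity, be aware of group assignment". The principal investigators, the statistician and the data collectors are to stay blinded. Section 6.2.2 places the treatment randomisation at Visit 2, at most 7 days after Visit 1.

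**The concern.** There are two problems. First, the protocol gives two incompatible rules for generating the list, so a reader cannot tell which one was used. This matters for the analysis as well as the report: section 9.5 examines block as a random factor and keeps it in the model unless its variance is non-significant at 0.20. Block membership therefore has to be defined.

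Second, the smallest possible fixed block is the most predictable permuted-block scheme for three arms. The trial runs at one site, and its coordinator and providers cannot be blinded. If the next arm can be foreseen, the timing of Visit 2 or a judgement at screening can be influenced by it. The resulting imbalance at entry would carry into NPR and RMDQ, which are self-reported, and blinded assessment afterwards would not remove it.

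**Working it through.** The documents state no predictability figure and give no derivation of the block size, so there is nothing to reproduce. The inputs are three arms, equal allocation, 162 patients in all, and the block sizes quoted above.

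**Fixed blocks of 3.** Each block holds one patient per arm.

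- Certain assignments: the third in each block follows from the first two, so 1/3 = 33.3%. In complete blocks this is 162/3 = 54 assignments. The planned sizes fit complete blocks: 42/3 = 14, 60/3 = 20, and for Experiment 2 by sex 33/3 = 11 and 27/3 = 9.
- Best guess: right with probability 1/3 at the first position, 1/2 at the second and 1 at the third. The mean is (1/3 + 1/2 + 1)/3 = 11/18 = 61.1%. Chance alone gives 33.3%.

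**Blocks of 6, size known.** Enumerating all permuted blocks gives 1/5 = 20.0% certain and 101/180 = 56.1% guessed correctly.

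**Blocks of 3 or 6.** The documents give no mix, so the two sizes are assumed equally likely for each block.

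- Sizes known, weighting by patients: certain (3 × 1/3 + 6 × 1/5)/9 = 2.2/9 = 24.4%; guessed (3 × 11/18 + 6 × 101/180)/9 = 5.2/9 = 57.8%.
- Sizes hidden, all past assignments in the stratum known: simulation of an observer who updates the probability of each block size, 6,000 runs each. Strata of 21 patients give 7.9% certain and 57.1% guessed; strata of 30 give 8.2% and 57.3%.

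| Rule | Certain in advance | Best guess correct |
|---|---|---|
| Fixed 3 (sections 3, 4.3) | 33.3% | 61.1% |
| 3 or 6, sizes known | 24.4% | 57.8% |
| 3 or 6, sizes hidden (section 9.2) | about 8% | about 57% |

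The gain is mostly in certainty, which falls about fourfold; guessing falls by only about 4 percentage points. The gain also depends on hiding the sizes: when they are known, 24.4% of assignments remain certain.

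**The coordinator.** These figures describe someone who infers the next arm from past ones. Whoever works from the table can read it, which is 100% under either rule. The documents shown describe no sealed envelopes, central release or third-party holder.

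**The case against.** The strongest reply is that the opportunity to act on a prediction is narrow. Visit 2 must follow Visit 1 within 7 days, or the candidate is re-screened and re-consented under a new ID. At the planned 3.4 patients a month spread over six strata, the expected number of other same-stratum arrivals in 7 days is (3.4/6) × (7/30.4) = 0.13, a chance of about 12%. With one experiment open it is (3.4/2) × (7/30.4) = 0.39, about 32%. Providers are blinded to the hypotheses, and the coordinator takes no part in the outcome assessments. These points stand and limit the likely bias. They do not settle which list was generated or conceal the list.

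A reader might also infer more than the documents support.

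- **That clinicians and participants know every assignment.** Section 5.2 says only that each participant knows their own arm, and contact between participants is minimised. A provider knows the patients he or she treats; no passage says that one provider sees them all or follows the sequence within a stratum. Only the coordinator is shown to know every assignment.
- **That the same clinicians screen and treat.** The Visit 1 examination forms are for a clinician, but nothing says this is the treating provider.
- **That the coordinator can choose the experiment, and so the list.** The enrolment form makes availability depend partly on whether "the study participant and laboratory schedules align", which leaves some discretion. But sections 3 and 9.2 use an adaptive randomisation when a candidate qualifies for more than one open experiment.

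Finally, the point comes late. The supplemental appendix reports 31 of 33 women and 18 of 27 men already tested in Experiment 2, and the June 2016 correspondence calls the study almost complete for participants with back pain.

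**Conclusion.** The contradiction is plain and lies in current text. If the fixed rule was followed, one assignment in three was certain, and 61.1% could be guessed, by anyone who knew the block size and the stratum's history. The section 9.2 rule lowers this to about 8% and 57%, provided the sizes are hidden and assuming they are equally likely. For the coordinator the block size is not the issue: as written, that role screens, schedules and assigns from the table, so every upcoming arm can be known. Nothing in the documents shows that entry was in fact steered, and no such claim is made here. The point deserves correction, but its effect at this stage is limited to the remaining slots, the block term in the model, and an accurate account of the method.

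**What to change.** 1. State one rule in sections 3, 4.3 and 9.2: the variable blocks of 3 or 6 that section 9.2 already contains, in random order, with sizes not disclosed to the coordinator or the treatment providers.
2. Have the list held by someone with no part in screening or scheduling, and release each assignment singly, only at Visit 2. This step is needed as well as the first, because variable blocks alone conceal nothing from a person who has the table.
3. Apply both to the remaining slots.
4. Record which block rule generated the strata already filled, so that the block random effect in section 9.5 is coded correctly and the report describes what was done.

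The cost is a wording amendment, a regenerated list for the open slots and a custodian for it. The statistical downside is small: an unfinished block of 6 holds at most two of any arm, so arms within a stratum can end up to two apart, against one for an unfinished block of 3. Where very few slots remain (33 − 31 = 2 women in Experiment 2 at the time of the appendix), a block of 6 cannot be completed; there, steps 2 and 4 matter most.

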## 4. SELECTION AND ENROLLMENT OF PARTICIPANTS

### 4.1 Inclusion Criteria

Participants must meet all of the following inclusion criteria to participate in this study:

- Between 18 to 45 years of age.
- Answer yes to the following questions
  - Have you had low back pain constantly or on most days for the last three months?
  - Has your back pain caused you to seek care or consultation from a health care provider?
- Average pain intensity, assessed using the Numerical Pain Rating (NPR) scale over the past week  $\geq 2$  on a 0-10 numerical pain scale
- Roland Morris Disability Questionnaire score  $\geq 4$
- Exhibit 3 of 4 of the following findings reported in the clinical prediction rules for spinal manipulation
  - No symptoms distal to the knee
  - FABQ work subscale score  $<19$
  - At least 1 hypo-mobile lumbar spinal segment
  - At least 1 hip  $> 35$  degrees internal rotation range of motion
- Exception: Participants in the healthy control group must report no low back pain (i.e., 0 rating on NPR, 0 score on Roland Morris Disability Questionnaire, and answer “No” to the following question: Have you had low back pain in the past 1-year that interrupted work/play or caused you to seek care from a healthcare provider?)

### 4.2 Exclusion Criteria

To be eligible for the study participants must not:

- Have a personal history of the following neurological disorders: Alzheimer’s, Amyotrophic Lateral Sclerosis, Multiple Sclerosis, Parkinson’s, Stroke
- Have a personal history of the following cardiorespiratory disorders: Congestive heart failure, Heart attack in past 24 months
- Have a personal history of the following musculoskeletal disorders: Rheumatoid Arthritis, pathologic fractures of the spine, avascular necrosis or osteonecrosis, severe osteoarthritis. Including a history of spine surgery or a hip arthroplasty
- Have active cancer
- Be Blind
- Have used narcotics or muscle relaxants within 30 days prior to study enrollment.
- Report being pregnant, lactating, or that they anticipate becoming pregnant in the next 3-months
- Have a body mass index greater than 35 kg/m^2
- Have clinical depression (i.e., subjects who score 24 or higher on the Center for Epidemiology Depression Scale).
- Report unexplained weight loss over the past month ( $>10$  lbs).

- Report they have pending litigation related to an episode of LBP or are receiving any type of disability services related to low back pain.
- Report having received any manual therapy intervention applied to the spine 30 days prior to first study intervention.
- Current drug or alcohol use or dependence that, in the opinion of the PIs, would interfere with adherence to study requirements.
- Applies to Experiment 3 (Cortical Effects) only: Have a personal or family history of epilepsy or seizures, Migraine Headaches within 6 months (186 days) of V2 physiologic testing, or taking medications in the benzodiazepine class.
- Applies to Experiments 1 and 3 (Muscular Effects and Cortical Effects) only: Have contraindications for exposure to a magnetic field.
- Applies to Experiment 1 (Muscular Effects) only: Have a positive result from pregnancy test administered the day of each MRI.

The supplemental research will enroll an additional 60 healthy participants with no history of LBP and who are matched on sex, age ( $\pm 3$  years), height ( $\pm 2$  inches), and weight ( $\pm 10$  lbs) to the participants recruited into **Experiment 2** of the RELIEF study. The same exclusion criteria are applied to the control group as is used for the RELIEF study LBP participants.

